**Vitamin D dosing for the main phase of then study:**

Based on the findings from the pilot phase of the study we have received IRB approval for the optimal safe dose of vitamin D where patient will receive stratified dose of vitamin D3 according to age. That is 20,000IU vitamin D3 in children <6 months, 50,000 IU in children 6-12 months and 100,000 IU in children 13-59 months of age on first day and thereafter 10,000 IU for next 4 days.

**Randomisation and Allocation Concealment**

The eligible children will be allotted a sequential study number, which will have been previously assigned to vitamin D3 or placebo in accordance with the randomisation. A computer generated random list will be developed by a person not involved in the study in any way. Participants and the research staff will be blinded to allocation. Pharmaceuticals Company will prepare the supplements off-site using individual opaque glass vials labeled with concealed unique identifiers for vitamin D3 and placebo. Allocation concealment will be done by sealed envelope and will be kept in a secured place by the person not associated with the study in any way; the envelope will be opened at the end of the study only, prior to data analysis.

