For the study, participants will be randomly assigned to one of two masked parallel intervention groups, with allocation concealment: vitamin D3 (cholecalciferol) or matched placebo. The vitamin D3 will be a high- concentration (20,000 IU D3 per mL) liquid formulation (Vigantol Oil, Merck KGaA, Germany), and the placebo will be miglyol oil 812 (Sasol, Germany), the vehicle used in Vigantol Oil. These active supplement and selected placebo are identical in appearance and both are tasteless. We have added vigantol oil and miglyol oil in 50 ml of “Milk Suji”, infant formula and expressed breast milk and there was no difference in appearance, color, odor or taste of diets with Vigantol oil (vitamin D3) or miglyol oil (placebo).

The allocated intervention, vitamin D3/placebo will be administered by adding in the diets within two hours of the first dose of parenteral antibiotics on the day of admission after confirming baseline ionized calcium within normal range and in the first morning diet for days 2-5 of the hospitalisation. Children who are unable to take oral diet, in that case vitamin D3/placebo will be administered through nasogastric tube with their diet. Intervention will be repeated if the child has vomiting within 30 minutes of intervention.

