**Monitoring during hospital stay**

#### During the 5 days of hospital stay data will be recorded 8 hourly including pulse and respiratory rates, axillary temperature, chest auscultatory findings, presence/absence of lower chest wall in drawing, oxygen saturation, and history of cough and feeding (Annexure 3). Resolution of sever pneumonia will be defined as absence of all signs of severe pneumonia, such as lower chest wall in drawing, cyanosis, hypoxia or lethargy, convulsion and inability to feed. Resolution of pneumonia will be considered when there is no fever, tachypnoea (RR less than 40 in children above 1 year and RR less than 50 in children below 1 year) for at least 24 hours and the child can be orally fed.

We will also monitor any adverse events suspected for vitamin D3 during hospital stay. Vitamin D3 at normal doses usually has no side effects. Any sign symptoms of vitamin D toxicity such as vomiting, decreased appetite, irritability, constipation, dehydration, fatigue, muscle weakness39  will be monitored and if recorded will be evaluated for hypercalcaemia. If hypercalcaemia develops we will stop further intervention with vitamin D/placebo. Any deterioration of child’s condition such as septic shock, apnoea (cease of respiration for 10-15 seconds) or cardiac arrest requiring the support of bubble CPAP or mechanical ventilation at any time of the study the child will be transferred to ICU and stop further intervention with vitamin D/placebo. And they will receive the standard hospital care and will be reported to ERC (Ethical Review Committee)/DSMB (data safety and monitoring board) as a case of SAE (serious adverse event). Proportion of such children in the two study groups will be compared during data analysis. We will assess serum “25 (OH)D”andcalcium level on admission. If calcium is above the safety level as mentioned above we will discontinue further intervention and exclude the child from the study.

We will also measure the amount of vitamin D patient received through dietary source (infant formula/milk suji) by calculating the total amount of milk received during hospital stay and there by the amount of vitamin D in International Unit (IU) in that amount of diet.

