## Data Safety Monitoring Plan (DSMP)

Data will be accessible to the PI, co-investigators, study physician and members of IRB. All the activities in this study will be closely monitored by PI and Co PIs. However a data safety and monitoring board (DSMB) will be there to meet at regular intervals for the monitoring of safety issue on vitamin D toxicity and any serious adverse event will be reported to the board.

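### Read literally, the rule for opening the allocation envelope leaves no direct way to learn what one child received if toxicity is suspected or a serious adverse event occurs

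*Protocol*

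**What the plan says.** The main phase is double blind: children are "randomly assigned to one of two masked parallel intervention groups", vitamin D3 or matched placebo (Study Intervention). Under Randomisation and Allocation Concealment, "Participants and the research staff will be blinded to allocation". The same section says that the sealed allocation "will be kept in a secured place by the person not associated with the study in any way", and that "the envelope will be opened at the end of the study only, prior to data analysis".

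The safety sections expect events during the trial. Under Monitoring during hospital stay, staff look for "Any sign symptoms of vitamin D toxicity such as vomiting, decreased appetite, irritability" and other signs, and evaluate the child for hypercalcaemia. The response is fixed: "If hypercalcaemia develops we will stop further intervention with vitamin D/placebo". A child who deteriorates goes to intensive care, the product is stopped, and the case is reported to the ethics committee and the safety board as a serious adverse event. The Data Safety Monitoring Plan has the board "meet at regular intervals for the monitoring of safety issue on vitamin D toxicity" and receive serious adverse events. None of these sections mentions breaking a code.

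**The concern.** The protocol does more than leave code breaking unmentioned. It states when the envelope is opened, adds the word only, and places the envelope with someone outside the study. A site following the text would have no authority to open one child's allocation, and neither the treating physician nor the board would have a stated route for asking.

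At stake is the assessment of single events. Whether a raised calcium or a serious event in one child is plausibly due to vitamin D depends partly on whether that child received it. The protocol itself says that little is known about the mechanisms of toxicity, and it makes a safe dose one of its secondary objectives. The effect estimate and the power are not affected.

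**Working it through.** The protocol gives no figure to reproduce. The check is a reading of the sections side by side, plus the arithmetic of exposure.

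**1. Is there an exception anywhere?** The sections on intervention, randomisation, baseline collection, hospital monitoring, safety monitoring and ethics, and the case report form, were read for any provision on individual unblinding. None has one. The only sentence on opening the code is the one in Randomisation and Allocation Concealment.

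**2. Which actions need the code?** Under Monitoring during hospital stay, hypercalcaemia and deterioration both lead to stopping vitamin D or placebo alike. These actions need no knowledge of the arm.

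**3. What remains once dosing has ended?** Dosing runs over days 1 to 5. Collection of Baseline Information schedules 25(OH)D and calcium again two weeks after discharge, and Follow up runs to 6 months. An event in that period cannot be answered by stopping a product already completed. The open question is past exposure, and the envelope stays sealed until the study ends, which is at least until the last child's follow-up is complete.

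**4. What exposure is in question?** The main-phase dosing section gives a first-day dose by age (20,000 IU under 6 months; "50,000 IU in children 6-12 months and 100,000 IU in children 13-59 months of age on first day"), then 10,000 IU on each of 4 days. Scheduled total = first-day dose + 4 × 10,000 IU:

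| Age | First day (IU) | Days 2–5 (IU) | Total (IU) |
| --- | --- | --- | --- |
| under 6 months | 20,000 | 40,000 | 60,000 |
| 6–12 months | 50,000 | 40,000 | 90,000 |
| 13–59 months | 100,000 | 40,000 | 140,000 |

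The placebo contributes none. A dose is repeated after vomiting within 30 minutes, so the amount given can exceed these totals. Both arms also receive some vitamin D in the diet.

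**5. What indirect information exists?**
- *Assays.* 25(OH)D and calcium are measured on admission and at day 5 or earlier discharge. The sample two weeks after discharge appears in Collection of Baseline Information. It does not appear in the main-phase schedule in Study Intervention or among the case report form's laboratory items, so it is not certain that a late result will exist.
- *Group field.* The case report form records allocation group as A or B. This separates the arms without saying which is vitamin D. The protocol does not say when the field is completed.
- *Clinical signs.* Vomiting, poor appetite, irritability and dehydration can also occur in acutely ill children with pneumonia, and children with diarrhoea are eligible. These signs discriminate poorly.

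**6. How many codes might be opened?** The protocol gives no event rate and does not state a chosen total sample size. As an illustration only, take the largest row of its sample-size table, 155 per group: 2 × 155 = 310 children. If 1% to 3% had an event prompting a request (assumed), that is 0.01 × 310 = 3.1 to 0.03 × 310 = 9.3, or about 3 to 9 children.

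**The case against.** The strongest reply is that the sentence concerns the release of the randomisation list. It sits under allocation concealment, speaks of one envelope, and ties the opening to data analysis. On that reading the protocol is merely silent on emergencies, and the procedure could sit in a board charter or an unblinding procedure. That reading is possible, so the point is put as what the text says literally. The text still contains the word only and no exception, and a site has no basis in the protocol for reading one in.

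A reader might infer that nobody can learn the exposure before the end. The documents do not support that. The ethics section gives hospital physicians and board members access to laboratory results, and a before-and-after pair of 25(OH)D values following doses of this size is informative. It remains indirect, because baseline status and dietary intake vary, and no section makes the assay a substitute for the code.

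A reader might also infer that the board could see toxicity only as a rate pooled over both arms. That does not follow either: if the A/B field is filled in during the trial, the board can tabulate by coded group with the envelope still sealed.

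It is also fair that no action written in the protocol changes with the allocation. The benefit is therefore confined to assessing individual events. Finally, a code break has a cost: the protocol describes no outcome assessors separate from ward staff, and pneumonia status is recorded on the inpatient form. That objection stands.

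**Conclusion.** The point holds as a minor one. Read literally, the envelope rule bars opening any single child's allocation during the main phase, and it has not been reconciled with the sections that foresee hypercalcaemia, serious adverse events and toxicity monitoring. The gap is the lack of a direct route to one child's allocation, chiefly after day 5. It does not prevent stopping the product, and it does not leave the board without group-level information.

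The exposure in question is 60,000 to 140,000 IU by age stratum; the top figure applies only to ages 13–59 months. The number of children concerned is unknown, and 3 to 9 rests on an assumed event rate and an assumed total of 310. The conclusion assumes that no separate unblinding procedure exists outside the protocol. It does not extend to the pilot, where both groups received vitamin D3.

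**What to change.** Reconcile Randomisation and Allocation Concealment with Monitoring during hospital stay and the Data Safety Monitoring Plan by stating that:

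- the off-study holder keeps one sealed code per study number;
- a single code may be opened for a serious adverse event or suspected toxicity, on a documented request from the treating physician or the safety board;
- each opening is logged with date, reason and recipient;
- the result is kept, as far as possible, from staff who record pneumonia status;
- the child stays in the intention-to-treat analysis;
- the full list stays sealed until analysis.

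The change needs a short paragraph and individual code slips. The downside is that a few children become unblinded. An opening during the hospital stay could also unblind the recording of the primary outcome for that child, so such cases should be identifiable in the log. An opening after severe pneumonia has resolved no longer threatens the primary outcome, but it could reach those recording new episodes in follow-up, and the same restriction should apply to them.

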**Definition of severe pneumonia**

Children aged 3 months to 59 months will be diagnosed as a case of severe pneumonia if they have a history of cough and/or respiratory difficulty plus oxygen saturation < 90% or central cyanosis, or severe respiratory distress (grunting, very severe chest in-drawing), or signs of pneumonia with a general danger sign (inability to breastfeed or drink, lethargy or reduced level of consciousness, convulsions), auscultatory findings of decreased or bronchial breath sounds or signs of pleural effusion or empyema.36

If a child presents with severe malnutrition (children with pitting oedema or Z scores below -3 standard deviations (SD) from the median for weight for height or weight for age or height for age) with any sign of pneumonia (any of the WHO defined signs of pneumonia or severe pneumonia or radiological pneumonia) would be considered as severe pneumonia.37

**Collection of Baseline Information**

All children within the defined age group suspected to have ALRI will be screened for study eligibility. Parents/ attending care givers of those fulfilling the eligibility, in application of the inclusion and the exclusion criteria, will be invited to provide their consent for enrollment of their children in the study. Upon signing a written informed consent, after providing information about the study and its interventions, possible benefits and risks, and voluntary nature of participation along with the right to withdraw children at any time after the initial consent without providing any reason, children will be enrolled. Case Record Form (CRF, ANNEXURE 1) will be used to collect relevant information such as medical history including nature and duration of illness, medication for current illness; socio-demographic characteristics such as sex, religion, gestational age, parental age with education, parents occupation, fuel use and smoking history, monthly family income, number of siblings, number of rooms, and cooking in bed room. Information will also be collected about child’s feeding practice such as history of breast feeding, formula or other complementary feeding, and immunisation status; family history of tuberculosis, recent respiratory tract infection of any family members and past history of child’s pneumonia, and history of exposure of the child to sun would be recorded. Medical examination findings to be recorded include pulse and respiratory rate, axillary temperature, anthropometric measurement, chest auscultation findings, chest wall in drawing, oxygen saturation, presence of cyanosis, and mental status (normal, irritable, lethargic). Weight of each child will be measured by electronic weighing scale with a precision of 0.1 kg and height/length will be measured using a locally made length board with precision of 0.1cm. Fever will be defined when the axillary temperature is 38C or greater. Respiratory rate will be counted for full 60 seconds by exposing the trunk when the child is awake and calm, and presence of lower chest wall in drawing will be noted at the same time. Respiratory rate will be counted for two times and if they differ by more than 5 breaths per minute then a third reading will be made, and the average of two closest respiratory rates (not deviating by 5 or greater number) will be regarded as the actual rate. Oxygen saturation will be measured using a Pulse Oxymeter (Nellcor Puritan Bennett Inc. N-560, Made in Korea) with a probe on a finger or toe when the child breathes in room air. Oxygen saturation of 90% or lesser will be defined as hypoxia which will be the indication for oxygen therapy. Chest X-ray will be done after enrollment and at discharge; however, it may be done at other times if clinically indicated. Five milliliter (5.0 mL) of venous blood will be collected from the children after enrollment in the study for estimation of complete blood count, C reactive protein, blood glucose, electrolytes,

“25 (OH)D”level, Ca, phosphorus, alkaline phosphatase, as well as blood culture for bacterial pathogen before the introduction of IV antibiotics and 2 ml venous blood will be collected at discharge and after 2 weeks of discharge for serum “25 (OH)D”and Ca level assay.

We will also monitor parathormone level randomly every fifth patients on admission and at discharge during the main phase of the study.

**Monitor ionized calcium level instead of total serum calcium:**

We will do blood test for serum ionized calcium instead of total serum calcium for the main phase of the study. In our pilot phase of the study we have found about 50% of our enrolled children with severe pneumonia were severely malnourished. These children may have low albumin level and so may not reflect the actual calcium status of the body through total serum calcium. Moreover ionized calcium gives more accurate picture of calcium in blood comparing to total serum calcium.

In that case as we have considered the upper normal limit of total serum calcium for safety monitoring, in case of ionized calcium the upper limit (normal range: 1.15-1.33 mmol/L)38 will be considered for safety monitoring. So the child having ionized calcium above 1.33mmol/L on admission will be stopped from having further intervention and excluded from the study.

**Treatment of Severe Pneumonia**

The enrolled children will be admitted to the Respiratory Ward of the Dhaka Hospital and placed on bed. Patency of their airway will be assessed and naso-and/or oropharyngeal suction will be given to those requiring them. Oxygen will be administered to those with an oxygenation saturation of 90% or lesser while breathing in room atmosphere. After the initial collection of a blood sample children will be treated according to pneumonia treatment guidelines of the Dhaka Hospital (Community Acquired Pneumonia in Children, Document No. PR/TG/006/00) added in Annexure 4.

**Monitoring during hospital stay**

#### During the 5 days of hospital stay data will be recorded 8 hourly including pulse and respiratory rates, axillary temperature, chest auscultatory findings, presence/absence of lower chest wall in drawing, oxygen saturation, and history of cough and feeding (Annexure 3). Resolution of sever pneumonia will be defined as absence of all signs of severe pneumonia, such as lower chest wall in drawing, cyanosis, hypoxia or lethargy, convulsion and inability to feed. Resolution of pneumonia will be considered when there is no fever, tachypnoea (RR less than 40 in children above 1 year and RR less than 50 in children below 1 year) for at least 24 hours and the child can be orally fed.

We will also monitor any adverse events suspected for vitamin D3 during hospital stay. Vitamin D3 at normal doses usually has no side effects. Any sign symptoms of vitamin D toxicity such as vomiting, decreased appetite, irritability, constipation, dehydration, fatigue, muscle weakness39  will be monitored and if recorded will be evaluated for hypercalcaemia. If hypercalcaemia develops we will stop further intervention with vitamin D/placebo. Any deterioration of child’s condition such as septic shock, apnoea (cease of respiration for 10-15 seconds) or cardiac arrest requiring the support of bubble CPAP or mechanical ventilation at any time of the study the child will be transferred to ICU and stop further intervention with vitamin D/placebo. And they will receive the standard hospital care and will be reported to ERC (Ethical Review Committee)/DSMB (data safety and monitoring board) as a case of SAE (serious adverse event). Proportion of such children in the two study groups will be compared during data analysis. We will assess serum “25 (OH)D”andcalcium level on admission. If calcium is above the safety level as mentioned above we will discontinue further intervention and exclude the child from the study.

We will also measure the amount of vitamin D patient received through dietary source (infant formula/milk suji) by calculating the total amount of milk received during hospital stay and there by the amount of vitamin D in International Unit (IU) in that amount of diet.

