**Outcome measures/variables:**

Primary outcome measure will be time to resolution of severe pneumonia.

Secondary outcome measures will be duration of hospitalization, fever, tachypnoea, chest in drawing, hypoxia, lethargy and inability to feed during hospital stay and as well as new episode of pneumonia after discharge.

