BCG 1= Yes, 2=No , 3=Don’t know, 9=NA

Penta 1 1= Yes, 2=No, 3=Don’t know, 9=NA

Penta 2 1= Yes, 2=No, 3=Don’t know , 9=NA

Penta 3 1= Yes, 2=No, 3=Don’t know, 9=NA

Oral polio 4 1=Yes, 2=No, 3=Don’t know, 9=NA

MR 1= Yes, 2=No, 3=Don’t know, 9=NA

Measles 2 1=Yes, 2=No, 3=Don’t know, 9=NA

42. Whom did you consulted first for this episode of illness of your child?

(1= qualified doctor, 2= homeopath doctor 3= spiritual adviser

4= quack, 5= drug seller, 6=traditional healer, 7= others, 8=none)

43. Why delay (if any)?

(1= financial constraint, 2= to take care at home, 3= under treatment of quack

4= under homoeopath or spiritual treatment, 5= could not realise the problem

6= single at home, 7= others, 9=not applicable)

44. a. Use of antibiotics before admission in hospital

(1=yes, 2=no, 3=don’t know, 4=not applicable)

b. Name of antibiotic used before admission in hospital

(1=Amoxycillin, 2=Cefixime, 3=Azythromycin, 4=Ciprofloxacin, 5=Ceftriaxone

6=Cefpodoxime, 9=Don’t know)

45**. Symptoms on admission**

| **Symptoms** | **1 = yes / 2 = no** | **Duration in days** |
| --- | --- | --- |
| Diarrhoea  (Type of diarrhea:1=AWD,2=ID,3=PD) |  |  |
| Cough |  |  |
| Running nose |  |  |
| Fever |  |  |
| Vomiting |  |  |
| Respiratory distress |  |  |
| Poor oral intake |  |  |
| Lethargy |  |  |
| Convulsion |  |  |
| Others 1 |  |  |
| Others 2 |  |  |
| Others 3 |  |  |
| Others 4 |  |  |

46.**Clinical Examination**

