**Follow up During Hospital Stay**

| Days | Date | Time | Pulse/min | Resp rate  /min | Chest indrawing | Spo2  (%) | | Temp  (◦C) | Lungs  (1=fine creps  2=coarse creps  3=clear) | Cough | Feeding  (1=well 2=poor) | Lethargy | Convulsion | AWD | Sign symtomps of Raised ICP | Pneumonia status* |
| --- | --- | --- | --- | --- | --- | --- | --- | --- | --- | --- | --- | --- | --- | --- | --- | --- |
| **Day 1** |  |  |  |  |  |  |  | |  |  |  |  |  |  |  |  |
| 0 hrs |  |  |  |  |  |  |  | |  |  |  |  |  |  |  |  |
| 8 hrs |  |  |  |  |  |  |  | |  |  |  |  |  |  |  |  |
| 16 hrs |  |  |  |  |  |  |  | |  |  |  |  |  |  |  |  |
| 24 hrs |  |  |  |  |  |  |  | |  |  |  |  |  |  |  |  |
| **Day 2** |  |  |  |  |  |  |  | |  |  |  |  |  |  |  |  |
| 8hrs |  |  |  |  |  |  |  | |  |  |  |  |  |  |  |  |
| 16 hrs |  |  |  |  |  |  |  | |  |  |  |  |  |  |  |  |
| 24 hrs |  |  |  |  |  |  |  | |  |  |  |  |  |  |  |  |
| **Day 3** |  |  |  |  |  |  |  | |  |  |  |  |  |  |  |  |
| 8 hrs |  |  |  |  |  |  |  | |  |  |  |  |  |  |  |  |
| 16 hrs |  |  |  |  |  |  |  | |  |  |  |  |  |  |  |  |
| 24 hrs |  |  |  |  |  |  |  | |  |  |  |  |  |  |  |  |
| **Day 4** |  |  |  |  |  |  |  | |  |  |  |  |  |  |  |  |
| 8hrs |  |  |  |  |  |  |  | |  |  |  |  |  |  |  |  |
| 16 hrs |  |  |  |  |  |  |  | |  |  |  |  |  |  |  |  |
| 24 hrs |  |  |  |  |  |  |  | |  |  |  |  |  |  |  |  |
| **Day 5** |  |  |  |  |  |  |  | |  |  |  |  |  |  |  |  |
| 8hrs |  |  |  |  |  |  |  | |  |  |  |  |  |  |  |  |
| 16hrs |  |  |  |  |  |  |  | |  |  |  |  |  |  |  |  |
| 24 hrs |  |  |  |  |  |  |  | |  |  |  |  |  |  |  |  |

(Pneumonia status* 1=severe pneumonia continues, 2=severe pneumonia resolved, 3=pneumonia continues, 4=pneumonia resolved)

| Days | Date | Time | Pulse/min | Resp rate/min | Chest indrawing | Spo2  (%) | Temp  (◦C) | Lungs  (1=fine creps  2=coarse creps  3=clear) | Cough | Feeding  (1=well 2=poor) | Lethargy | Convulsion | AWD | Sign symtomps of Raised ICP | Pneumoia status* |
| --- | --- | --- | --- | --- | --- | --- | --- | --- | --- | --- | --- | --- | --- | --- | --- |
| **Day 6** |  |  |  |  |  |  |  |  |  |  |  |  |  |  |  |
| 0 hrs |  |  |  |  |  |  |  |  |  |  |  |  |  |  |  |
| 8 hrs |  |  |  |  |  |  |  |  |  |  |  |  |  |  |  |
| 16 hrs |  |  |  |  |  |  |  |  |  |  |  |  |  |  |  |
| 24 hrs |  |  |  |  |  |  |  |  |  |  |  |  |  |  |  |
| **Day 7** |  |  |  |  |  |  |  |  |  |  |  |  |  |  |  |
| 8hrs |  |  |  |  |  |  |  |  |  |  |  |  |  |  |  |

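### Duration of inability to feed cannot be derived from the case report form, which codes feeding only as well or poor

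*Protocol*

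**What the plan says.** The Protocol uses inability to feed in three places.

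- Definition of severe pneumonia: the general danger signs at entry are "inability to breastfeed or drink, lethargy or reduced level of consciousness, convulsions".
- Monitoring during hospital stay: resolution of severe pneumonia requires that all its signs are gone, "such as lower chest wall in drawing, cyanosis, hypoxia or lethargy, convulsion and inability to feed". Under Outcome measures/variables, "Primary outcome measure will be time to resolution of severe pneumonia".
- Secondary objectives and Outcome measures/variables: the secondary durations end with "lethargy and inability to feed during hospital stay".

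The case report form annexed to the Protocol collects something else. The grid headed Follow up During Hospital Stay has one feeding column, coded 1 for well and 2 for poor. Item 45, on admission symptoms, has a line for "Poor oral intake". No field in the form as shown records inability to feed or drink, or feeding by tube.

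The same grid has an overall code entered at each check: "Pneumonia status* 1=severe pneumonia continues, 2=severe pneumonia resolved, 3=pneumonia continues, 4=pneumonia resolved".

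**The concern.** The outcome is defined on one state and the form records a broader one. Reduced intake and inability to feed differ in severity, and only the second is a danger sign in the Protocol's own definition. If the form does not separate them at the bedside, the distinction is lost for good: 8-hourly observations cannot be regraded after discharge, and no rule in an analysis plan can restore them. At stake is whether one named secondary outcome can be reported as defined, and whether the feeding component of the primary event can be verified.

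**Working it through.** The documents give no figure for how often children feed poorly without being unable to feed, so the check is a comparison of definitions with form fields.

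**1. Sign-duration outcomes against the grid.** The secondary outcomes include six sign durations.

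| Duration outcome | Grid column |
| --- | --- |
| Fever | Temperature |
| Tachypnoea | Respiratory rate |
| Chest indrawing | Chest indrawing |
| Hypoxia | SpO2 |
| Lethargy | Lethargy |
| Inability to feed | Feeding: well or poor only |

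Five of the six have a matching column. Inability to feed does not.

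**2. What the feeding column can give.** If every child who cannot feed is coded poor, then for each child

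T(coded poor) = T(unable to feed) + T(feeds poorly but able).

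Only the left side is recorded. The outcome is the first term on the right, and it cannot be separated from the second. At best the recorded duration is an upper bound.

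**3. Even the upper bound is not assured.** The Study Intervention section treats children who cannot take food by mouth as a separate state and doses them by nasogastric tube. The grid has no code for that state. A child tolerating tube feeds could be coded well, in which case the period of inability is missed. Misclassification can therefore run in both directions.

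**4. Whether the two states are likely to differ here.** About half of the pilot children were severely malnourished (section on monitoring ionized calcium), and children with diarrhoea are eligible. Both could plausibly reduce intake without inability to feed. This is an inference; no rate is given.

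**5. The primary event.** The status code lets the assessor record at each check that severe pneumonia has resolved. Nothing in the Protocol says that this code is computed from the feeding column. The event can therefore be captured, but its feeding component cannot be audited: a status of resolved beside a feeding code of poor could be correct or an error, and the form cannot show which.

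**6. Overlap with toxicity.** Monitoring during hospital stay lists as signs of vitamin D toxicity "vomiting, decreased appetite, irritability, constipation, dehydration, fatigue, muscle weakness". Appetite loss from the study drug would be coded poor in the grid, in the same way as persisting illness. That is a route to arm-dependent misclassification. Its size depends on the rate of such appetite loss and on how often feeding is the last sign to clear, and the documents give neither.

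**The case against.** The strongest reply is that the primary event has its own field. A blinded assessor can apply the full definition of resolution at the bedside, including whether the child can feed, without following the feeding code. That stands. What is left for the primary endpoint is a gap in traceability.

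A reader might infer more: that resolution is mis-scored and the trial loses power, or that vitamin D is penalised because drug-related appetite loss counts as persisting disease. The documents support neither. Any power loss would need assumed shares of affected children and assumed delays, and it would also assume that chest indrawing, hypoxia, lethargy and convulsion had already cleared. On the drug effect, the Protocol says that side effects are unusual at normal doses and reports that two earlier trials saw no toxicity symptoms. Item 48 of the form already records decreased appetite by dosing day. Any such bias would also work against vitamin D and could not create a false benefit.

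Two smaller replies also carry weight. Item 45 describes admission symptoms and does not feed the in-hospital duration. Cyanosis, a listed component of resolution, has no grid column, but SpO2 is recorded at every check, so that gap is minor.

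Finally, the monitoring text refers to Annexure 3 while the form shown is headed Annexure 2, and completion instructions that might define poor are not shown. The finding therefore holds for the form as shown. A definition of poor in such instructions would still leave one code for two states, unless poor were restricted to inability to feed.

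**Conclusion.** The point holds for the secondary outcome. Duration of inability to feed, one of eight secondary outcomes, cannot be derived from the form as shown; only duration of poor feeding can. This needs no numerical assumption.

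For the primary endpoint the conclusion is narrower: resolution can still be captured through the status code, but its feeding component cannot be checked against the written definition.

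Arm-dependent misclassification is possible and not shown. Its size cannot be computed from the documents, so no effect on power or on the treatment estimate is claimed. The problem is modest in scope, but it cannot be repaired once the data are collected.

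**What to change.** Recode the feeding column of the 8-hourly grid:

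- 1 = feeds well
- 2 = feeds poorly but able to breastfeed or drink
- 3 = unable to breastfeed or drink, including children fed by tube for that reason

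Add one sentence to Monitoring during hospital stay stating that only code 3 counts as inability to feed, both for the secondary duration and as the feeding component of resolution of severe pneumonia. The status code can then be checked against the recorded signs.

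A yes/no cyanosis column is an optional minor addition.

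The cost is one recoded column, one sentence and brief retraining of ward staff. No visit, test or treatment rule changes.
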